## **8.2 Statistical Analysis Plan (SAP)**

Prior to database lock and before code breaking, a final version of the SAP shall be issued and approved by the study statistician, and the principal investigator. The SAP will define all 'pre-specified, planned analyses' and provide the general specifications for the analysis of the data to be collected and presented in the Clinical Study Report.

## **9. Ethical principle**

For every study center, only when the trial protocol is approved by the Investigational Review Board (IRB), the enrollment of participant will begin, but all should be after April 27, 2013.

## **10. Funding**

This study is supported and funded by the Beijing Foundation for Science and Technology of Traditional Chinese Medicine (JJ2011-03).

## **11. Update on the Published Protocol**

As compared to the published protocol (Zhang XZ, Zhang L, Guo J, et al. Acupuncture as prophylaxis for menstrual-related migraine: study protocol for a multicenter randomized controlled trial. *Trials*. 2013;14:374), the present finalized study protocol had made several amendments because of practicality.

(1) language revision of outcomes for precision presentation and readers' better understanding:

- a, 'The change of migraine days inside the menstrual cycle' was revised to 'The change from baseline in average number of migraine days per perimenstrual period';
- b, 'The change of migraine days outside the menstrual cycle' was revised to 'The change from baseline in average number of migraine days per outside perimenstrual period';
- c, 'Duration of migraine attack' was revised to 'The change from baseline in mean migraine hours during/outside perimenstrual period';
- d, 'Visual analogue scale (VAS) for pain' was revised to 'The change from baseline in mean pain VAS during/outside perimenstrual period';
- e, 'The proportion of responders (defined as the proportion of patients with at least a 50% reduction of the number of menstrual migraine days)' was revised to 'The proportion of participants with at least 50% reduction from baseline in number of migraine days';
- f, 'Intake of acute medication' was revised to 'The proportion of participants using acute pain medication'.

(2) Major amendments for mistake correction or better presentation (Table 1):

**Table 1.** Major update of the published protocol

| No. | Item            | Published version                                                                                                                                                                                                                                                                                                                                                                                                                                                              | Final version                                                                                                                                                                                                                                                                                                                                                                                                                                                                  |
|-----|-----------------|--------------------------------------------------------------------------------------------------------------------------------------------------------------------------------------------------------------------------------------------------------------------------------------------------------------------------------------------------------------------------------------------------------------------------------------------------------------------------------|--------------------------------------------------------------------------------------------------------------------------------------------------------------------------------------------------------------------------------------------------------------------------------------------------------------------------------------------------------------------------------------------------------------------------------------------------------------------------------|
| 1   | Study design    | Follow-up phase: 1 month.                                                                                                                                                                                                                                                                                                                                                                                                                                                      | Follow-up phase: 3 cycles (Cycle-4 to Cycle-6).                                                                                                                                                                                                                                                                                                                                                                                                                                |
| 2   | Sample size     | According to the previous pilot study, the number of migraine days after treatment in acupuncture group is $3.1 \pm 2.7$ days, and the control group is $5.2 \pm 4.4$ days. Based on 0.8 power to detect a significant difference( $\alpha = 0.01$ , two-sided), 73 participants will be required for each group, which is calculated by PASS 2008. Allowing for a 20% withdrawal rate, we will plan to enroll a total of 184 participants with 92 participants in each group. | According to the previous pilot study, the number of migraine days after treatment in acupuncture group is $3.1 \pm 2.7$ days, and the control group is $5.2 \pm 4.4$ days. Based on 0.9 power to detect a significant difference( $\alpha = 0.05$ , two-sided), 68 participants will be required for each group, which is calculated by PASS 2008. Allowing for a 20% withdrawal rate, we will plan to enroll a total of 172 participants with 86 participants in each group. |
| 3   | Randomization   | The central randomization will be performed by the Research Center of Clinical Epidemiology affiliated to Peking University in China, which use block randomization to generate the random allocation sequence and prepare predetermined computer made randomization opaque sealed envelopes.                                                                                                                                                                                  | We randomly assigned each participant to acupuncture or medication groups via a central randomization system using a 1:1 ratio, which was performed by the Research Center of Clinical Epidemiology affiliated to Peking University. Randomization was stratified by centers with a fixed block size of 4.                                                                                                                                                                     |
| 4   | Primary outcome | a. The change of migraine days inside the menstrual cycle
b. The proportion of responders (defined as the proportion of patients with at least a 50% reduction of the number of menstrual migraine days).                                                                                                                                                                                                                                                                   | Change from baseline in average number of migraine days per perimenstrual period over cycles 1-3.                                                                                                                                                                                                                                                                                                                                                                              |

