## **2.4 Methodology**

### **2.4.1 Trial design**

This is a multicenter, double-dummy, participant-blinded, randomized controlled clinical trial at 4 centers in China.

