#### **2.4.1.1 Randomization**

This study, we will use blocks randomization, stratified according to center. A central randomization system will be applied in our trial. The randomizing scheme will be produced by staff of the Research Center of Clinical Epidemiology affiliated to Peking University using statistical analysis software SAS9.4 with “proc plan” program. After production, it will be signed and sealed by the staff who produce it and keep by other staff who take no part in this trial. It will not be allowed to be checked by anyone except the top system administrator. Acupuncturists in each center will be responsible for getting random numbers. Via inputting the participants’ sex and birthday in the central randomization system through the phone or the web, they will get the random number.

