#### **2.4.2.4 Subject Recruitment, Screening and Group Assignment**

Two strategies will be used to recruit participants with MRM. One is to recruit participants in outpatient clinics from the four centers mentioned above. The other is to show recruitment posters outside the clinics. Research assistants of each center will preliminarily screen the participants by recording their disease condition, history of the disease and treatment, and the demographic data. Experienced neurologist in each trial center will take charge of the diagnosis of MRM. Potential participants will receive a 3-cycle baseline assessment, during which they have to fill out headache diaries. Eligible participants then will be randomized to acupuncture or medication group. Acupuncturists will be in charge of participant assignment, and the trial procedures. Acupuncturists and neurologists will be responsible for the assessment of safety during treatment, including the acupuncture-related

AEs or medication-related adverse events (AEs). During the trial, independent evaluators of each center will instruct the participants how to fill in their headache diaries. The evaluators will record the data on the case report form (CRF) through the whole trial period. The subject flow was shown in **Figure 1**.

[figure not shown]

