### **4. Interventions**

The intervention scheme of this trial will be based on expert consensus and result of

previous pilot study(23). There will be 1 full-time acupuncturists per center (4 acupuncturists in total in 4 centers) responsible for operation of acupuncture and sham acupuncture. In general, acupuncturists will be assigned to the same participants throughout the 3-cycle treatment schedule, except for vacation conflicts and staff turnover. All acupuncture treatments were delivered by acupuncturists who were registered with Ministry of Health of the People's Republic of China with more than 20 years of clinical experience. Sterile disposable steel acupuncture needle (size: 0.25 mm×25 mm for head points, 0.3 mm×40 mm for limb and abdomen points, Hwato Needles, made in Suzhou, China) will be used in this trial. It took 9 cycles in total for a patient to complete the trial, 3 cycle's baseline assessment, 3 cycle' treatment, and 3 cycle' follow up.

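### Fixed blocks of 4 within centre, with the unblinded acupuncturist requesting allocations, leave up to about one third of assignments predictable if the block size is known or inferred

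*Supplement*

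**What the plan says.** Protocol section 2.4.1.1 gives the method without a block size: "we will use blocks randomization, stratified according to center". The size and ratio appear only in the final-version column of Table 1 in section 11, where allocation is described as "via a central randomization system using a 1:1 ratio" and the table adds: "Randomization was stratified by centers with a fixed block size of 4".

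Three passages place the request for an allocation with the person who gives the treatment:
- Section 2.4.1.1: "Acupuncturists in each center will be responsible for getting random numbers". The only inputs to the system that it names are the participant's sex and date of birth.
- Section 2.4.2.4: "Acupuncturists will be in charge of participant assignment, and the trial procedures".
- Section 4: "There will be 1 full-time acupuncturists per center". This person gives both the true and the sham needling. Cover for vacation and staff turnover is allowed.

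Section 2.4.1.2 lists participants, outcome assessors and statisticians as blinded. Acupuncturists are not on the list. They could not be, because the two arms are needled at different points (sections 4.1 and 4.2). Section 6 relies on the central system for protection against selection bias.

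**The concern.** Sealing the list and releasing numbers by phone or web stops anyone from reading ahead. It does not stop someone from deducing the next assignment from those already made. Because blocking is within centre, the sequence that a centre's acupuncturist sees is exactly the sequence that is forced to balance every four assignments.

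Someone who can foresee the next arm could influence which eligible woman is randomised next, or when. The arms could then differ in severity or in expectation of benefit. The outcomes are diary-based and reported by the participants. The primary model adjusts for the baseline value (SAP 6.3.3), which removes only the part of such a difference that this covariate captures.

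**Working it through.** **Inputs.** Block size 4, ratio 1:1, stratified by centre (protocol section 11, Table 1); four centres (section 2.4.1); 172 participants (section 2.4.1.3). The plan gives no predictability figure to reproduce, and 172 is used only as the number of assignments. Centre sizes are not stated. Equal centres of 172/4 = 43 is an assumption.

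**Step 1: certain assignments.** A 1:1 block of 4 has 6 equally likely orders. An assignment is certain once one arm has used both of its places.
- Positions 1 and 2: never certain.
- Position 3: certain if the first two were the same arm, which is 2 orders of 6 = 1/3.
- Position 4: always certain.

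Expected number per block = 0 + 0 + 1/3 + 1 = 4/3, so the share is (4/3)/4 = 1/3.

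**Step 2: scale to the trial.**
- All blocks complete: 172/4 = 43 blocks, and 43 × 4/3 = 57.3 assignments (33.3%).
- Four centres of 43: each has 10 complete blocks and 3 places of an eleventh. That gives 10 × 4/3 + 1/3 = 13.67 per centre, 4 × 13.67 = 54.7 in all, and 54.7/172 = 31.8%.

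**Step 3: best guess.** Always guess the arm that is behind, and toss a coin when the arms are level. The chance of being right at positions 1 to 4 is 1/2, 2/3, 2/3 and 1.
- Complete blocks: (1/2 + 2/3 + 2/3 + 1)/4 = 2.833/4 = 70.8%.
- 43 per centre: (10 × 2.833 + 1/2 + 2/3 + 2/3)/43 = 30.17/43 = 70.2%.
- Chance alone: 50%.

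**Step 4: effect of varying the block size.** Simulation at 43 per centre, for an observer who knows the set of sizes and all past assignments but not the order of the sizes:

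| Block sizes | Certain | Best guess right |
|---|---|---|
| fixed 4 | 31.8% | 70.2% |
| 4 or 6 at random | 5.9% | 68.6% |
| 4, 6 or 8 at random | 2.4% | 67.4% |

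A hand check on the last row: over complete blocks, expected correct guesses are 2.833 of 4, 4.1 of 6 and 5.329 of 8. Equally frequent sizes give 12.262/18 = 68.1%, close to the simulated value, which includes incomplete last blocks. Varying the size therefore removes nearly all certainty but little of the guessing advantage, because guessing the arm that is behind needs no knowledge of the block size.

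**The case against.** The strongest reply is that nothing shows the sites knew the block size. Section 2.4.1.1 omits it, and the earlier published text, as reproduced in section 11, says only "which use block randomization to generate the random allocation sequence". The size stands in one table cell written in the past tense. The final protocol cites a 2015 paper, while section 9 allows enrolment from after 27 April 2013, so the disclosure may post-date the start of recruitment. This stands, and it makes the one-third figure conditional. It does not remove the risk: about 43 allocations per centre is roughly ten blocks, each balancing after four, so an attentive acupuncturist could infer the size.

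There are also real safeguards. The list is sealed and open only to the top system administrator. Research assistants screen, a neurologist makes the diagnosis, and a three-cycle diary baseline comes before randomisation (section 2.4.2.4). By then the woman has consented and her baseline has been recorded, which narrows the room for selection. What is missing is any statement that eligibility is fixed in the system before a number is issued, so influence over order or delay is not excluded. That acupuncturists have discretion over timing is itself an inference from their role; no section grants it.

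A reader might infer that concealment is defeated, or that one person obtains every allocation at a centre. The documents support neither. About two thirds of assignments stay uncertain even to someone who knows the block size, and section 4 allows for cover staff.

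**Conclusion.** The point holds as a weakness of the set-up. Fixed blocks of 4 within centre, with an unblinded acupuncturist requesting allocations and no stated eligibility lock, leave up to about one third of assignments certain in advance (54.7 to 57.3 of 172) and a best guess that is right about 70% of the time. These are upper figures. They assume that the acupuncturist knows or infers the block size and tracks past assignments, and the lower count also assumes four centres of 43. That acupuncturists are unblinded is inferred from their task and from their absence from the blinded list.

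The central system therefore does not by itself give the protection against selection bias that section 6 claims for it. A reader might go further and conclude that selection occurred or that the result is biased. The documents contain no evidence of that.

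**What to change.** 1. Generate the list with randomly varying block sizes within centre, for example 4, 6 and 8, and keep the sizes out of every document that sites hold. This needs a small change to the PROC PLAN code and one sentence in section 2.4.1.1. The cost is a slightly larger possible imbalance within a centre: the largest possible difference at any moment is half the block size, so it rises from 2 to 4.
2. Have the central system release an allocation only after eligibility and the baseline diary are recorded and locked, and say so in section 2.4.1.1. Since varying the sizes leaves best-guess accuracy at about 67%, this step matters at least as much as the first.
3. If another existing staff member makes the request, send the code only to the acupuncturist. Research assistants check the diaries (section 2.4.4.1) and neurologists assess adverse events (sections 2.4.2.4 and 3), so showing them the allocation would create an unblinding problem in place of the concealment problem.
4. If randomisation is already complete, disclose the block size and who requested allocations. Add a baseline comparison between positions whose assignment was certain and the other positions, shown by arm, since steering could act in opposite directions in the two arms. This needs only the randomisation list in order and the baseline data.

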## 1. Introduction

Menstrual migraine can be divided into two subtypes: pure menstrual migraine (PMM) and menstrually related migraine (MRM), with most of the cases being MRM. MRM is defined as attacks of migraine without aura, occurring between days -2 to +3 of the menstruation in at least two out of three menstrual cycles, with additional attacks of migraine at other times of the cycles by the International Classification of Headache Disorders (ICHD). More than 50% of female patients report that their migraines are associated with the menses. Attack onset is usually before the age of 20 years, with peak prevalence between the ages of 25 and 55 years, declining with menopause. Increasing evidence links menstrual migraine to the female sex hormones. Most of the data in the literature report that MRM causes significant limitations of daily activities (for example, nausea, vomiting, and photo-phonophobia), and the attacks are generally longer, more severe, and less drug-responsive than non-menstrual ones. The options available for the treatment of MRM include acute therapy and prophylaxis (short-term preventive therapy and long-term preventive therapy). Acute therapy is initiated first. As MRM is unique in its predictability, treatment can be targeted to the period of time when patients are most likely to experience migraine. The treatment window for menstrual migraine occurs between 2 days before and 3 days after the onset of menses. The goals of prophylactic strategies are to reduce attack frequency, severity and duration, improve responsiveness of treatment for acute attacks, improve function, and reduce disability. Prophylactic medications include non-steroidal anti-inflammatory drugs, triptans, estrogen, magnesium, dihydroergotamine, methysergide, and vitamin E. Caution should be taken when the drug is used within the same month for treating migraine attacks occurring during perimenstrual period and outside perimenstrual period due to the risk of medication-overuse headache, a risk which is, however, common to all medications used for menstrual-migraine prophylaxis or treatment. Several studies have already reported the encouraging results in the therapy for migraine by acupuncture. When reviewing the evidence of acupuncture for MRM, only one published randomized controlled trial could be found. However, because of the limited evidence, high-quality RCTs are needed to assess the efficacy of acupuncture as the preventive treatment for

MRM.

## **2. Study Objective**

The primary objective is to evaluate the efficacy of acupuncture as the preventive treatment for menstrually related migraine.

## **3. Design**

### **3.1 Overview**

This multicenter, participant-blinded, randomized controlled clinical trial will be performed to demonstrate the safety and efficacy of acupuncture as the preventive treatment for MRM.

### **3.2 Inclusion/Exclusion Criteria**

#### **3.2.1 Inclusion Criteria**

1. Diagnosis of MRM: MRM without aura (code A1.1.2), in which migraine without aura always occurs on days  $1 \pm 2$  of menstruation in at least two out of three menstrual cycles, and at other times due to different triggering factors or for no apparent specific reason (International Classification of Headache Disorders-second edition [ICHD-II]);
2. Regular menstrual cycle(25-35 days);
3. Could predict within three days both the onset of menstruation and perimenstrual migraine attacks;
4. Repeated migraine attacks, frequency of non-menstrual migraine is more than once a month;
5. Written informed consent.

#### **3.2.2 Exclusion Criteria**

1. Chronic migraine, tension-type headache, cluster headache, and other primary headaches;

2. Secondary headache and other neurological diseases;
3. Relatively severe systemic diseases (cardiovascular disease, acute infectious disease, hematopathy, endocrinopathy, and allergy);
4. Headache caused by otorhinolaryngology diseases or intracranial pathological changes;
5. Oral contraceptives, pregnancy, or lactation period;
6. Use of prophylactic migraine medication in the last 3 months;
7. Participation in another clinical trial.

#### 4. Study Schema

|                                        | STUDY PERIOD |            |           |    |    |           |    |    |
|----------------------------------------|--------------|------------|-----------|----|----|-----------|----|----|
|                                        | Baseline     | Allocation | Treatment |    |    | Follow-up |    |    |
| VISIT                                  | 1            | 0          | 2         | 3  | 4  | 5         | 6  | 7  |
| TIMEPOINT(C, cycle)                    | -3-0C        |            | 1C        | 2C | 3C | 4C        | 5C | 6C |
| Enrollment                      |              |            |           |    |    |           |    |    |
| Screening                              | ×            |            |           |    |    |           |    |    |
| Informed consent                       | ×            |            |           |    |    |           |    |    |
| Eligibility criteria                   | ×            |            |           |    |    |           |    |    |
| Demography
Characteristics          | ×            |            |           |    |    |           |    |    |
| Disease history of MRM                 | ×            |            |           |    |    |           |    |    |
| Laboratory test                        | ×            |            |           |    | ×  |           |    |    |
| Randomization                          |              | ×          |           |    |    |           |    |    |
| Interventions                   |              |            |           |    |    |           |    |    |
| True acupuncture plus placebo naproxen |              |            | ×         | ×  | ×  |           |    |    |
| Sham acupuncture plus true naproxen    |              |            | ×         | ×  | ×  |           |    |    |
| Assessments                     |              |            |           |    |    |           |    |    |
| Headache diary                         | ×            |            | ×         | ×  | ×  | ×         | ×  | ×  |
| Migraine days                          | ×            |            | ×         | ×  | ×  | ×         | ×  | ×  |
| Migraine hours                         | ×            |            | ×         | ×  | ×  | ×         | ×  | ×  |
| VAS                                    | ×            |            | ×         | ×  | ×  | ×         | ×  | ×  |
| ≥50% migraine responder rate           | ×            |            | ×         | ×  | ×  | ×         | ×  | ×  |
| Intake of acute pain medication        | ×            |            | ×         | ×  | ×  | ×         | ×  | ×  |

|                          |   |   |   |         |       |   |   |   |
|--------------------------|---|---|---|---------|-------|---|---|---|
| Assessment of blinding   |   |   |   | ×(1.5C) | ×(3C) |   |   |   |
| Participant's compliance |   |   | × | ×       | ×     |   |   |   |
| Adverse events           | × | × | × | ×       | ×     | × | × | × |

MRM: menstrually related migraine; VAS: visual analogue scale.

